### Sample size

To minimize contamination and simplify project management, we will use one-stage clustered sampling. For a two-sided significance level of 0.05 and power of 80%, the sample size is calculated for both the binary variable Drug Compliance (DC) and the continuous variable Drug Compliance Score (DCS), with DC referring to a patient outcome achieving pre-defined compliance or not, while DCS refers to a score anywhere from 0 (no compliance) to 10 (full compliance), calculated as the proportion of the number of drugs actually taken by an individual divided by the number of drugs prescribed for that individual over a given period of time. As our previous study of Project 686 patients with schizophrenia in Liuyang Municipality showed a 50% compliance rate, or DC of 0.5, our calculations were based on the need to detect DC in the range of 0.5 (the current rate) to 0.7 (our hypothesized improvement). In conducting our sample size analysis, we used software developed by the University of Aberdeen, U.K., specifically for clustered randomized trials [19].

### Sample size with the binary variable drug compliance (DC)

For a cluster randomized trial, the sample size must be ‘inflated’ over that of an individual randomized controlled trial (IRCT), taking into consideration the size of the cluster as well as the intra-cluster correlation coefficient (ICC). As we are uncertain about the ICC and the effect size associated with our intervention, we did a further sensitivity analysis (as shown in Table 1) on the minimum effect size detectable in relation to various sample sizes and ICCs, assuming a 5% significance level and 80% power.

**Table 1 T1:** Sample size with binary DC

**Proportion of patients achieving DC in the control group****	**Proportion of patients achieving DC in the treatment group**	**ICC**	**Number of clusters needed***
0.5	0.6	0.01	86
		0.05	114
		0.1	148
0.5	0.7	0.01	22
		0.05	28
		0.1	36
0.5	0.8	0.01	10
		0.05	12
		0.1	16

*The exercise uses a 5% significance level at a power of 80%, with 10 patients per cluster as suggested by Project 686 registries.

**The control group proportion of patient achieving DC is based on our current research in Liuyang.

From the table above, we can see that in order to detect a minimum increase in the proportion of patients achieving DC from 0.5 to 0.6, we will need a sample of at least 860 patients, even assuming a liberal ICC of 0.01. However, if we can achieve a minimum increase of 0.5 to 0.7, even at a conservative ICC of 0.1, only 360 patients are needed for this increase to be detectable. Assuming a patient drop-out rate of 10%, we arrive at a sample size of 400 patients. Project 686 records indicate that villages in the cluster have an average of 10 patients per village; consequently, 40 villages will be needed to gather a sample of 400 villagers with schizophrenia.

### Sample size with the continuous variable drug compliance score (DCS)

The continuous variable DCS will also be used in our data analysis. Our current research in Liuyang indicates a mean DCR score under Project 686 of 7 out of a total score of 10; for a significance level of 0.05 at a power of 80%, and a conservative ICC of 0.1, 38 villages with a total of 380 individuals will be a sample sufficient to detect an effect as small as an increase of 1 in the DCS score. Given the likelihood of drop-outs, we will include 2 additional villages for a total of 40 containing 400 individuals. Once 40 villages have been selected at random, they will be further randomized into 20 villages in the treatment group and 20 in the control group.

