### Instruments

Four types of statistics will be collected at baseline and at 6 months and 12 months into the study:

Socio-demographic characteristics: age, sex, education level, marital status, work, economic status, domestic situation (living alone, with family, or with friends).

Clinical characteristics: years of illness, number of bed days in psychiatric hospital in previous two years.

Compliance: This is our primary dependent variable measure. The binary variable Drug Compliance (DC) will be recorded by interviewing patients and their family members. We define as ‘compliant’ patients who, over the past month, have taken all pills as prescribed; otherwise, patients are recorded as ‘non-compliant.’ We will report 1-month, 3-month, 6-month and 12-month compliance as the proportion of patients achieving compliance over the total number of patients. In addition, a continuous variable Drug Compliance Score (DCS) will be used to measure medication compliance. The DCS score will be measured by dividing the actual number of pills taken by the total number of pills prescribed multiplied by 10 over a given period of time, with scores ranging from 0 (complete non-compliance) to 10 (complete compliance). For example, if a patient over the past month took 20 pills out of 100 prescribed, his compliance will be (20/100) × 10 = 2 for the past month.

Clinical/outcome measures: Four types of measures will be collected.

Symptoms score: Schizophrenia is often described in terms of positive and negative (or deficit) symptoms. Negative symptoms respond less well to medication [20], particularly to the antipsychotics that are typically used for cases in our research. Therefore, we will concentrate on the positive symptoms as these correlate more strongly with medication compliance. The Brief Psychiatric Rating Scale (BPRS) will be used to evaluate positive symptoms. The BPRS is an 18-item rating scale that has been widely used in psychiatric practice and research in China, and has good to excellent reliability and validity.

Social functions: We will use the global assessment of functioning (GAF) scale, in which a score of 0 to100 is converted to a disability weight ([100-GAF score]/100). Patients with a disability weight of 0.40 or greater are classified as moderately to severely disabled.

Quality of life score: We will use the QALY weights developed by Lenert *et al*. [21].

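### The 38-village figure for a 1-point DCS increase needs an SD of about 2.5, but the plan's own compliance figures imply about 3.0 or more, giving roughly 65–68% power at best for an unadjusted score comparison

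*Protocol article*

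**What the plan says.** In the Protocol article, *Sample size* sets a two-sided 5% level and 80% power for both compliance outcomes. It reports that the group's previous study in Liuyang "showed a 50% compliance rate, or DC of 0.5", and it hypothesises 0.7 under the intervention. The Table 1 footnotes give 10 patients per village and attribute the control proportion to current research in Liuyang.

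*Sample size with the continuous variable drug compliance score (DCS)* gives a "mean DCR score under Project 686 of 7 out of a total score of 10", also from current research in Liuyang. At an ICC of 0.1, it claims that "38 villages with a total of 380 individuals will be a sample sufficient to detect an effect as small as an increase of 1" point. Two villages are then added for drop-out, making 40.

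*Instruments* defines compliant as "patients who, over the past month, have taken all pills as prescribed", and DCS as pills taken divided by pills prescribed, times 10. *Comparison between VD model and CAU model* analyses the change in DCS from start to end by OLS with covariates.

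**The concern.** An SD missing from a journal article is not a fault in itself. The difficulty is that the SD needed to obtain 38 villages appears to be smaller than the article's other figures allow. A patient who took every pill scores exactly 10. If half the patients are at 10 and the mean is 7, the other half must average 4, and that gap alone produces a large SD.

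DCS is part of the primary compliance measure and is the outcome in the only regression model written out. If the power claim is too high, a null DCS result may be taken as stronger evidence against a 1-point effect than the design supports. The chance of missing such an effect would be about one in three, not one in five.

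**Working it through.** **Inputs.** Two-sided alpha 0.05 and power 80% (*Sample size*), so (1.96 + 0.8416)² = 7.849. Ten patients per village (Table 1 footnote) and ICC 0.1 give a design effect of 1 + 9 × 0.1 = 1.9. Control DC 0.5, treated DC 0.7, mean DCS 7, difference 1. I read DCR in the DCS paragraph as DCS, since it is scored out of 10.

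**Check of method.** The usual two-proportion formula without continuity correction, times the design effect and rounded up to whole villages per arm, reproduces all nine entries of Table 1. For 0.5 v 0.7 at ICC 0.1: 93 × 1.9 = 176.7 per arm, so 18 villages per arm and 36 in total. A different formula is therefore unlikely to explain the DCS result.

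**SD behind the 38 villages.** Effective n per arm = 190/1.9 = 100. The SD that gives 80% power for 1 point is 1/(2.8016 × √(2/100)) = 2.52. Working forwards, SD 2.50 needs 2 × 7.849 × 6.25 = 98.1, rounded up to 99 per arm; 99 × 1.9 = 188.1, so 19 villages per arm and 38 in total. SD 2.40 gives 36 villages and SD 2.55 gives 40. The implied SD is about 2.5.

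**Smallest control SD.** Let a share p score 10 and the overall mean be 7. The variance is smallest when all the others share one value, and it then equals 9p/(1 − p).

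| Fully compliant share | Mean of the others | Minimum SD |
|---|---|---|
| 0.50 | 4.0 | 3.00 |
| 0.45 | 4.5 | 2.71 |
| 0.41 | 4.9 | 2.50 |
| 0.40 | 5.0 | 2.45 |

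At p = 0.5 the variance is 0.5 × 3² + 0.5 × 3² = 9. Any spread among the non-compliant raises it.

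**Smallest treated SD.** With DC 0.7 and mean 8, the others average (8 − 7)/0.3 = 3.33. Variance = 0.7 × 2² + 0.3 × 4.67² = 9.33, so SD ≥ 3.06. The pooled floor is √((9 + 9.33)/2) = 3.03.

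**Unadjusted power for 1 point, SD 3.0 in both arms.**
- 38 villages × 10: Φ(1/(3 × √(2/100)) − 1.96) = Φ(0.397) = 65.4%.
- 40 villages × 9 (10% drop-out): design effect 1.8, effective n = 180/1.8 = 100, so again 65.4%.
- 40 villages × 10: effective n = 200/1.9 = 105.3, power 67.7%.
- At the pooled floor of 3.03: 64.6% (38 villages) and 66.9% (40 villages).
- A t reference on villages minus 2 df lowers these slightly (63.1% for 38 villages at SD 3.0).

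Detectable difference at 80% power with effective n = 100: 2.8016 × 3 × √(2/100) = 1.19. Villages for 1 point at SD 3.0: 2 × 7.849 × 9 = 141.3, rounded up to 142; 142 × 1.9 = 269.8 per arm, so 27 villages per arm and 54 in total.

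To show that the floor is a best case: if the non-compliant were spread evenly over 0–8 (assumption), the variance is 9 + 0.5 × 64/12 = 11.67, SD 3.4, and power at 38 villages is 54%.

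**Planned change-score model.** With a baseline-to-end correlation r (not given), SD 3.0 at both times and ICC 0.1 also applied to the change (assumptions), the SD of change is 3√(2(1 − r)). With baseline DCS as a covariate the residual SD is 3√(1 − r²). Power at effective n = 100:

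| r | Change score | Baseline as covariate |
|---|---|---|
| 0.30 | 51% | 70% |
| 0.50 | 65% | 78% |
| 0.54 | 69% | 80% |
| 0.65 | 80% | 87% |
| 0.70 | 86% | 91% |

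**The case against.** A reader might infer that the DCS analysis can never have more than 65–68% power, or that an SD of 2.5 is impossible. The documents do not support either without conditions.

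- **Analysis.** The written model uses the change in DCS. Its power depends on r and, over r = 0.3 to 0.7, lies on both sides of the unadjusted figure. This stands. However, the DCS paragraph claims no gain from baseline data, and below r = 0.5 change scores reduce power.
- **One arm only.** The 50% and the mean of 7 bound only the control arm. If the treated mean rose to 8 with full compliance still at 50%, the treated floor would be 2.0, the pooled SD 2.55 and power about 79–81%. This is correct arithmetic, but it needs a 1-point gain with no rise in full compliance, against the hypothesised 0.7.
- **Same patients?** The 50% is credited in one place to a previous study and in the Table 1 footnote to current research; the mean of 7 comes from current research. The DCS recall period is left open, and nothing confirms that the earlier study used the all-pills definition. The Background section *Drug compliance* puts past-month daily use at under half, and calls this consistent with a study in which 60% did not comply. At about 41% or fewer fully compliant, 2.5 becomes attainable. This stands as a condition, but the sample size itself uses 0.5.
- **Pilot.** *Sample size validation* promises to test the assumptions on pilot data. Without a stated SD, the article gives no value to test.

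It is also tempting to score at 0 the roughly 30% of registered patients who had not collected their drugs, which would cut power much further. With a mean of 7 that forces the other 70% to score 10, which contradicts DC 0.5, so that scenario is not usable.

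**Conclusion.** The concern holds in a limited form. The stated 80% power needs an SD of about 2.5, which conflicts with DC 0.5, the all-pills definition and a mean of 7 taken together. For an unadjusted comparison of DCS scores, power for 1 point is about 65% (38 × 10, or 40 × 9 after drop-out) to 68% (40 × 10) at best, and 54 villages would be needed for the stated target.

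This rests on three assumptions: the 50% and the 7 refer to the same patients and recall period, the treated arm reaches the hypothesised DC of 0.7 at a mean of 8, and the ICC is 0.1. It is not a ceiling for the change-score model, which reaches about 80% if r is about 0.65 or more (about 0.54 with baseline DCS as a covariate).

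Nor does it show that the trial as a whole is underpowered. The binary calculation reproduces at 36 villages and independently leads to 40. This is a misstated power figure for one outcome, not a failure of the design.

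**What to change.** State the SD used, and whether it is of the score or of the change, taken from the existing Liuyang data or the pilot. If a gain from baseline data is relied on, state the correlation assumed. Confirm whether the 50% and the mean of 7 come from the same patients and period.

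Then restate the DCS sentence, for example: 40 villages give about 65% power for a 1-point difference in DCS, or 80% power for about 1.2 points (unadjusted, SD 3.0, ICC 0.1, 10% drop-out).

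The cost is one rewritten paragraph and a less favourable DCS figure. No villages are added, and the binary DC sample size stays as it is.

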### Intervention – VD model

In the VD model, village doctors will receive training in case-management of villagers with schizophrenia using a protocol developed in the pilot study. The three-day training will feature mental health knowledge, case-management skills, and directly observed therapy (DOT). The format will be tailored to the competencies and expectations of VDs. Family members of patients will receive four hours of psycho-educational coaching on how to support patients and cooperate with the village doctor. VDs will participate in the case management protocol for one year and will receive instruction on antipsychotic therapy from visiting psychiatrists at the time of bimonthly drug dispensing.

Specifics of the VD model are given below.

Per Project 686 protocol, psychiatrists dispense drugs, but provide no other services and do not engage family members in the care of patients. In our VD treatment model, VDs cooperate with Project 686 psychiatrists and also reach out to family members to manage patients and provide the following five services:

1. Develop and maintain case files for every schizophrenia patient.

2. Store and distribute antipsychotics to family members on a weekly basis, or directly observe drug-taking (DOT) at the village clinic on a daily basis.

3. Accompany patients and family members on bimonthly visits to psychiatrists for drug dispensation in order to participate in assessing patients’ mental status and explain treatment plans to patients and their families.

4. Record patients’ medication-taking behavior weekly.

5. Identify signs of relapse in order to provide prompt referral services.

To incentivize VDs’ participation, we have obtained preliminary approval to include VDs’ case management efforts in their annual performance review, and will provide a modest fee for VDs for their time and effort.

### Procedures

Following a pilot study (see Section below), 40 villages (excluding the pilot study villages) will be randomly selected in Liuyang Municipality. We will conduct a baseline survey of patients with schizophrenia in the villages, collecting data on social demographics, compliance rates, clinical characteristics, and outcome measures. Researchers will explain the research to participants and obtain written informed consent from both patients and family member. And after the randomization, VDs and family members of patients will receive training and education in the 12-month case management protocol as noted in Section above. Researchers will visit VDs every month during the first three months of the study and every three months thereafter for the remaining nine months of the study, obtaining feedback and giving follow-up instructions, and recording and monitoring VDs’ case management work via questionnaire.

In the CAU model, control villages will continue to receive bimonthly visits by psychiatric professionals, who will dispense free antipsychotics per existing Project 686 protocol. No other interventions will be introduced.

Follow-up interviews will be conducted with patients in both VD and CAU model villages at 6 months and 12 months into the intervention, collecting the same data as that collected at baseline (see below).

### Instruments

Four types of statistics will be collected at baseline and at 6 months and 12 months into the study:

Socio-demographic characteristics: age, sex, education level, marital status, work, economic status, domestic situation (living alone, with family, or with friends).

Clinical characteristics: years of illness, number of bed days in psychiatric hospital in previous two years.

Compliance: This is our primary dependent variable measure. The binary variable Drug Compliance (DC) will be recorded by interviewing patients and their family members. We define as ‘compliant’ patients who, over the past month, have taken all pills as prescribed; otherwise, patients are recorded as ‘non-compliant.’ We will report 1-month, 3-month, 6-month and 12-month compliance as the proportion of patients achieving compliance over the total number of patients. In addition, a continuous variable Drug Compliance Score (DCS) will be used to measure medication compliance. The DCS score will be measured by dividing the actual number of pills taken by the total number of pills prescribed multiplied by 10 over a given period of time, with scores ranging from 0 (complete non-compliance) to 10 (complete compliance). For example, if a patient over the past month took 20 pills out of 100 prescribed, his compliance will be (20/100) × 10 = 2 for the past month.

Clinical/outcome measures: Four types of measures will be collected.

Symptoms score: Schizophrenia is often described in terms of positive and negative (or deficit) symptoms. Negative symptoms respond less well to medication [20], particularly to the antipsychotics that are typically used for cases in our research. Therefore, we will concentrate on the positive symptoms as these correlate more strongly with medication compliance. The Brief Psychiatric Rating Scale (BPRS) will be used to evaluate positive symptoms. The BPRS is an 18-item rating scale that has been widely used in psychiatric practice and research in China, and has good to excellent reliability and validity.

Social functions: We will use the global assessment of functioning (GAF) scale, in which a score of 0 to100 is converted to a disability weight ([100-GAF score]/100). Patients with a disability weight of 0.40 or greater are classified as moderately to severely disabled.

Quality of life score: We will use the QALY weights developed by Lenert *et al*. [21].

Hospitalization rate: Time to readmission is measured by a product-limit formula. Hospitalization rate is the proportion of patients with schizophrenia who warrant hospital admission. Data on hospitalization will be collected from patient medical records.

Incidence of risky behavior: Risky behaviors in schizophrenia include suicide, self-harm, and wandering. We will collect incidence data from family members of patients as to the number of times the above-mentioned behaviors have occurred in the past year.

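### The 1-, 3-, 6- and 12-month compliance reports do not fit a past-month measure taken at baseline, 6 and 12 months; past-year risky behaviour at month 6 is half pre-intervention; DC and DCS are not ranked

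*Protocol article*

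**What the plan says.** **Timing of data.** Procedures states: "Follow-up interviews will be conducted with patients in both VD and CAU model villages at 6 months and 12 months into the intervention", and says that these interviews repeat the baseline data collection. Instruments likewise gives baseline, 6 and 12 months as the collection times.

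**Compliance.** Instruments names compliance as the primary dependent variable. DC is obtained by interviewing patients and family members; a patient is compliant if all pills were taken as prescribed over the past month. The section then says: "We will report 1-month, 3-month, 6-month and 12-month compliance as the proportion of patients achieving compliance over the total number of patients". DCS is added as a continuous measure over a period that is not fixed.

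**Contacts in months 1–3.** Procedures says: "Researchers will visit VDs every month during the first three months of the study". These visits concern the village doctors' case-management work. Under the VD model, village doctors also record medication-taking weekly. The Abstract says that control patients get no management or follow-up beyond the two-monthly psychiatrist visits.

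**Risky behaviour.** Family members report the "number of times the above-mentioned behaviors have occurred in the past year".

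**Bed days.** Instruments lists the "number of bed days in psychiatric hospital in previous two years" under clinical characteristics. Statistical methods uses the two-year figure as a measure of illness severity before the programme began.

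**Sizing.** Under Sample size, "the sample size is calculated for both the binary variable Drug Compliance (DC) and the continuous variable Drug Compliance Score (DCS"), at two-sided 0.05 and 80% power. Statistical methods compares both measures; its regression on change in DCS from start to end is labelled an example.

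**The concern.** The primary outcome is promised at four horizons, but the stated definition and schedule support only two. Analysts would have to decide later what 1-month and 3-month compliance mean. If they took them as time points, the only records from that period are kept by the people delivering the intervention, in one arm. If they took them as look-backs, a long window asked too early would count months that the intervention could not have influenced.

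The same problem affects risky behaviour at month 6. Each arm's count would include half a year of pre-randomisation experience, which pulls the comparison towards no difference.

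Finally, with two compliance measures under one primary heading, each sized at the full 5%, a reader cannot tell which result decides whether the trial succeeded.

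**Working it through.** **1. The plan's own sample size.** Inputs from Sample size with the binary variable DC: proportions 0.5 and 0.7 ("if we can achieve a minimum increase of 0.5 to 0.7"), ICC 0.1, 10 patients per village, two-sided 0.05, 80% power, 10% drop-out.
- Per arm, individually randomised (pooled variance, no continuity correction): [1.960·√(2·0.6·0.4) + 0.842·√(0.25 + 0.21)]² / 0.2² = 93.
- Design effect: 1 + (10 − 1)·0.1 = 1.9.
- Clusters per arm: 93·1.9/10 = 17.7, rounded up to 18. In total 36 clusters, or 360 patients.
- Drop-out: 360/0.9 = 400.

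This matches the article, and the other eight cells of Table 1 reproduce in the same way. The DCS figure of 38 villages cannot be checked because no standard deviation is given.

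**2. Which compliance results the schedule can supply**

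| Reported figure | As a time point, past-month DC | As a look-back at month 6 | As a look-back at month 12 |
|---|---|---|---|
| 1-month | No interview, either arm | After start | After start |
| 3-month | No interview, either arm | After start | After start |
| 6-month | Interview, both arms | After start | After start |
| 12-month | Interview, both arms | 6 of 12 months before start | After start |

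Past-month DC at the two follow-up interviews covers roughly months 5–6 and 11–12, so it cannot reach month 1 or 3. On the look-back reading, every row except the first departs from the past-month definition. For a 12-month all-pills-taken measure asked at month 6, a patient who missed a pill in the six months before the start cannot count as compliant.

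**3. Past-year risky behaviour.** Pre-intervention share f = max(0, window − visit month)/window.
- Month 6: (12 − 6)/12 = 0.50.
- Month 12: (12 − 12)/12 = 0.

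If the intervention halves the event rate from its start, and the pre-intervention rates are equal in the two arms, the observed rate ratio is f + (1 − f)·0.5. At month 6 this is 0.5 + 0.5·0.5 = 0.75. At month 12 it is 0.5, undiluted.

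**4. Two unranked measures.** If a significant result on either DC or DCS counted as success, familywise error is 1 − P(|Z₁| < 1.96 and |Z₂| < 1.96) for correlated standard normal statistics. The article gives no correlation, so it is assumed:

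| Assumed correlation | Familywise error |
|---|---|
| 0 (ceiling) | 9.75% |
| 0.80 | 7.8% |
| 0.90 | 7.0% |
| 0.95 | 6.5% |

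**5. Effect of a remedy on size.** Naming DC as the single primary leaves step 1 as it is: 400 patients. Splitting alpha at 0.025 each would raise 93 to 113 per arm. Then 113·1.9/10 = 21.5, rounded up to 22 clusters per arm; 44 clusters in all, 440 patients, and 440/0.9 = 489 after drop-out. With the planned 40 villages of 10, power for DC would fall from about 85% to 77%.

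**The case against.** **Look-backs need no extra visit.** Asked at the 12-month interview, all four windows lie within the intervention year in both arms, and the open period in the DCS definition is compatible with that. The article does not expressly say that a 12-month look-back is asked at month 6. This is a fair reading, and it points to one of the fixes. But it contradicts the past-month definition of DC, and because Procedures has the same data collected at each follow-up, nothing keeps the longer window out of month 6.

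**Primary results missing for controls.** A reader might infer that some primary results exist for the VD arm only. The documents do not support that. Neither arm has a patient interview at months 1 or 3, and past-month DC at 6 and 12 months is available in both. Only village-doctor records are one-sided.

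**Bed days.** A reader might also infer that two-year bed days are a diluted outcome, since 75% of the window at month 6 and 50% at month 12 precede the programme. That does not hold. Statistical methods deliberately defines them as a pre-programme severity covariate, and the hospitalisation outcome is described separately and drawn from medical records.

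**Risky behaviour.** The past-year window is correct at month 12 and parallels the baseline year, so an end-minus-start comparison is unaffected. Statistical methods also treats the outcome as binary, for which the rate formula is only approximate. Both points stand; the flaw is confined to month 6.

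**Multiplicity.** DC comes first, DCS is introduced as an addition, and error control is commonly left to an analysis plan. Sizing both at 5% is not a plan to claim success on either. This stands as far as the error rate is concerned, which is therefore conditional. What remains is that the article names a primary domain without choosing the measure, and its worked model uses DCS.

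**Conclusion.** The point holds in a limited form and should be corrected.

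- **Compliance horizons:** the text is faulty on either reading. This rests on the documents alone and needs no assumption.
- **Risky behaviour:** half the month-6 window is pre-intervention. The ratio of about 0.75 assumes a true halving of the rate from the start of the intervention and equal rates in the arms beforehand. Month 12 is sound.
- **Ranking:** DC and DCS are not ranked. The 6.5–8% familywise error rests on an assumed correlation of 0.8–0.95 and on an either-measure success rule that the article does not state. A higher figure, obtained by also treating months 6 and 12 as co-primary, has no basis in the text.

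The DC sample-size arithmetic is correct and is not touched by this point.

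**What to change.** 1. Name past-month DC at the 12-month interview as the single primary outcome, with DCS and the month-6 results secondary. The sample size stays at 400.
2. Either drop the 1- and 3-month time-point reports, or define every n-month compliance figure as a look-back lying wholly after the intervention starts, for example asked at the 12-month interview. Label these separately from past-month DC.
3. At month 6, ask about risky behaviours since baseline (six months). Keep the past-year question at baseline and month 12.
4. State that two-year bed days are a baseline-only severity covariate.

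The cost is an outcome-definition sentence and questionnaire wording, with no added patients or visits. According to Trial status, the study was still in its pilot phase. The one downside is that the month-6 risky-behaviour window is shorter than the baseline window, so at month 6 the arms should be compared directly or as rates, not as change from baseline counts.
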